### Data analysis

The equivalence of the two groups will be tested using *χ*^2^ tests of association for categorical variables and t-tests for quantitative variables. Variables on which the groups differ will be included as covariates in the analyses. Clustering by group will be accounted for in analysis by using Generalized Linear Mixed Model variations of logistic regression, linear regression, and Poisson regression [56]. Analyses of all aims will be conducted by two-tailed tests with alpha of .05. An intent-to-treat approach will be used so that subjects are considered to be in the condition to which they were randomized despite how much they actually used that type of care.

The primary focus for Aim 1 is on comparing the two interventions (Tobacco Tactics website and 1-800-QUIT-NOW control condition) in their effects on smoking cessation using 6-month self-report together with results of the 6-month cotinine test. Using an intent to treat analysis, participants who cannot be reached or who fail to return the cotinine strip will be considered to be still smoking. Analysis of this measure will be conducted by using logistic regression of quit rate adjusted for clustering to compare the quit rates of those in the intervention arm to those in the control arm. Percentage quitting by group will be presented as a descriptive statistic to characterize the difference in quit rates between the two groups. This analysis will be supplemented by logistic regressions with smoking status as the dependent measure, treatment group as the independent variable, adjusted for clustering, but also adding in any baseline measures that were found in preliminary analyses to differ between groups, power permitting. If baseline measures differ between groups, we will effectively equate the groups. The same kinds of clustered logistic regression analyses will also be conducted on a less definitive version of the outcome measure: the self-report whether or not it is confirmed by a cotinine test. This analysis has the advantage of a slightly larger number of quitters identified because some people who actually quit smoking may not want to send in a urine sample (even on a cotinine test strip) because they fear it might reveal other problems.

Since tobacco use reduction is a feasible first step towards improved health, another approach is to look at smoking reduction less than quitting. These analyses will be conducted for those who continue to smoke and look at the number of cigarettes/day smoked, quit attempts, and nicotine addiction (FTND). The first two of these are quantitative measures available at baseline and at follow-up so will be analyzed by multiple linear regression with baseline measures included as covariates again adjusting for clustering in group assignments. Other covariates will be controlled as needed. Quit attempts is a count variable which will be analyzed by a Poisson regression (designed for analysis of counts) with treatment condition as the independent variable, controlling for covariates as needed. For all the measures analyzed to meet Aim 1 significant differences in quit rates and the quantitative measures between the Tobacco Tactics group and the 1-800-QUIT-NOW group will indicate whether the Tobacco Tactics intervention is more effective in influencing quitting.

Some of the process measures (e.g., number of times each module is accessed) for Aim 2 are distinct for the two interventions so will simply be analyzed descriptively. On the other hand most of the process measures (e.g., contacts, medications used, and ratings of helpfulness with the intervention) are comparable across groups so will be analyzed both descriptively, and compared statistically between the two groups. The distributions of these measures cover the range from counts (potentially Poisson distributed) to ratings (potentially normally distributed). Distributions will be examined before selecting the appropriate analytic method for comparison of groups.

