### Theoretical framework

As in our prior studies, the theory guiding the Tobacco Tactics website intervention is the Health Belief Model [35]. This model proposes that behavior is influenced by Perceived Benefits (e.g., effectiveness of quitting smoking to reduce health risk and financial benefits), Perceived Barriers (withdrawal symptoms and other obstacles to quitting), Self-Efficacy (feeling of confidence that one can quit), Cues to Action (stimulus and reminders), by Perceived Susceptibility (chance of having negative health outcomes if continuing to smoke), and Severity of the Health Threat. Our current research has demonstrated that these characteristics are associated with 6-month quit rates and quit attempts.

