### Measures

#### Outcome evaluation (Aim 1)

To measure 30-day and 6-month cessation, we will ask participants in both groups if they have smoked cigarettes, even a puff, within the last 7 days [47]. Tobacco use status at 6 months will be confirmed by biochemical verification in the form of urinary cotinine test strips sent by mail. Harm reduction will also be assessed including cigarettes smoked/day, number of quit attempts, and nicotine addiction. Nicotine dependence will be assessed using the Fagerstrom Test for Nicotine Dependence (FTND) [48]. The Health Belief Model will be tested by questions (rated on a 5-point scale) used in our prior studies including: 1) Perceived Benefits: How important do you think quitting smoking is to your health? 2) Perceived Barriers: How difficult do you think it would be to quit smoking? and 3) Self-Efficacy: How confident are you that you will be able to stay off cigarettes? Based on current literature and pilot work done in this population, alcohol use [49], depression [50], stress [51], social support [52], comorbidities [53], and demographics [54,55] all may influence quit rates and therefore will be measured by valid and reliable instruments and controlled for as necessary in the analysis. Demographics have been shown to influence quit rates [54,55], so questions will be asked about age, gender, race, marital status, educational level, and veteran status.

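### Covariates are selected by unclustered tests of baseline differences, not fixed on prognosis, and the general rule conflicts with the first-line quit-rate model

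*Protocol article*

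**What the plan says.** Under Data analysis, the protocol article tests the equivalence of the arms with chi-square "tests of association for categorical variables and t-tests for quantitative variables". It names no allowance for clustering in these tests. The next sentence gives the general rule: "Variables on which the groups differ will be included as covariates in the analyses". Mixed models that allow for the training group are then specified for the regressions.

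The first-line analysis of cotinine-supported 6-month cessation in the same section is "logistic regression of quit rate adjusted for clustering to compare the quit rates of those in the intervention arm" with those in the control arm. It names no baseline covariate. A supplementary model follows, "adding in any baseline measures that were found in preliminary analyses to differ between groups, power permitting".

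Outcome evaluation (Aim 1) lists alcohol use, depression, stress, social support, comorbidities and demographics, which "all may influence quit rates and therefore will be measured by valid and reliable instruments and controlled for as necessary in the analysis". Theoretical framework says of the Health Belief Model constructs that "these characteristics are associated with 6-month quit rates and quit attempts". Neither section fixes a covariate for the quit-rate models.

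Randomization and access to the intervention states that everyone in a given training goes to the same arm. For the smoking-reduction outcomes, Data analysis does fix the baseline measure as a covariate in the linear models. Other covariates there, and those for the Poisson model of quit attempts, are left to need.

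**The concern.** There are three linked faults.

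- **Wrong criterion.** In a randomised trial, a small baseline p-value marks an imbalance that arose by chance. It says nothing about whether the variable predicts quitting. A strong predictor with a moderate imbalance can fail the screen, and an irrelevant variable with p < .05 can pass it.
- **Wrong unit.** The screening tests treat people as independent although sessions are allocated. If people within a session resemble each other, the tests flag differences too often.
- **Conflicting instructions.** The general rule places differing variables in the analyses without exception. The quit-rate paragraph keeps them out of the first-line model and puts them in a supplement, subject to a condition about power that has no threshold.

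At stake are an adjusted result whose content is decided by chance imbalance, and power that known predictors could have supplied in a trial planned at 80%.

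**Working it through.** **1. The plan's own figures.** The claim disputes no stated figure, but these set the scale. With 92 per group and a standardised difference of 0.5, power is 92.4% (normal) or 92.1% (noncentral t), which matches the stated 92% for Aim 2. For Aim 1 the control quit rate is not given. The stated 80% for a 16-point difference is reproduced at a control rate of 10% (n = 90 per group, power 81.2%) or 11% (n = 94, power 79.5%). At 15% v 31%, power is 73.6%.

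**2. How often the screen flags a truly balanced variable.** The article gives no separate level for the screen, so I take its general .05. The number of variables is a count from Outcome evaluation (Aim 1): 5 psychosocial or clinical plus 6 demographic items make 11. Adding the three belief items makes 14. Adding cigarettes/day, quit attempts and FTND makes 17. With independent tests, P(at least one) = 1 − 0.95^k:

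| k | Expected false flags (0.05k) | P(at least one) |
|---|---|---|
| 11 | 0.55 | 43% |
| 14 | 0.70 | 51% |
| 17 | 0.85 | 58% |

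**3. Effect of ignoring clustering.** Cluster size m and ICC are not stated, so both are assumed. Design effect DE = 1 + (m − 1) × ICC, and the true per-test error is 2 × [1 − Φ(1.96/√DE)]. For m = 10 and ICC = 0.05, DE = 1 + 9 × 0.05 = 1.45, 1.96/√1.45 = 1.63, and the error is 10.4%. The chance of at least one false flag is then 1 − 0.896^11 = 70% for 11 variables and 1 − 0.896^17 = 84% for 17. Over m = 5 to 20 and ICC = 0.01 to 0.10, the per-test error runs from 5.5% to 25%.

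**4. What the selection rule does to the treatment test.** The simulation used 92 per arm, 4,000 runs, assumed marginal quit rates of 15% v 31%, two prognostic and ten irrelevant covariates, and no clustering. The strength of the prognostic covariates is an assumption.

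| Log-OR per SD | Unadjusted | Prespecified prognostic | Test-selected |
|---|---|---|---|
| 0.5 | 73.2% | 76.0% | 73.0% |
| 0.7 | 73.6% | 79.3% | 73.3% |
| 1.0 | 75.6% | 85.7% | 76.3% |

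Prespecification gained 2.9, 5.7 and 10.1 points over no adjustment. Test selection stayed within 1 point of no adjustment. Under the null, all three strategies rejected between 4.0% and 5.1% of the time. At least one of the 12 covariates was selected in 46% to 47% of runs, which agrees with 1 − 0.95^12 = 46%.

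**5. How many covariates the data can carry.** Expected quitters are 92 × (0.10 + 0.26) = 33, or 92 × (0.15 + 0.31) = 42. Both pairs of rates are assumptions. With treatment and three covariates, that is 33/4 ≈ 8 to 42/4 ≈ 11 quitters per coefficient, so the list has to be short.

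**The case against.** The strongest reply is that the main result is largely untouched. The first-line quit-rate model contains no covariates, and the natural reading is that the specific paragraph governs, with the supplement carrying out the general rule. This stands. A reader might infer that the primary model itself is picked after looking at the data by arm, or that the plan has two rival primary estimates. The text does not go that far. It contains a general sentence that contradicts a specific one, and the two must be reconciled.

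A reader might also infer that the rule produces false positives. The simulation gives no support for that: error stayed at 4% to 5% under every strategy.

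Three further limits stand. Baseline values are already fixed in the linear reduction models. The number of sessions is not given, so it cannot be claimed that few sessions make imbalance likely. Baseline collection of the belief items is an inference: Recruitment and pre-intervention survey says the baseline survey covers tobacco use and covariates described later, while the belief items are listed under outcome evaluation.

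It can also be said that an article leaves the final covariate list to the analysis plan, and that "controlled for as necessary in the analysis" leaves prognostic variables open rather than excluded. As to a missing list, that is fair. It does not answer the point, because the article states a selection rule, states it twice, and the rule is a poor one that an analysis plan following the protocol would inherit.

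**Conclusion.** The point holds with limited reach. The stated rule selects covariates on chance imbalance, through tests that ignore how the trial was randomised. It affects the supplementary adjusted quit-rate model and the other outcome models that follow the general sentence. That sentence also conflicts with the clustering-only first-line model.

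The harm is arbitrary covariate choice and forgone power of about 3 to 10 points. That range rests on assumed covariate strengths, assumed quit rates of 15% v 31% and no clustering. The 43% to 58% chance of at least one false difference rests on independent tests at .05 and a count of 11 to 17 variables. It rises with any positive ICC, by an amount the article does not allow one to fix. An unadjusted primary model remains a defensible choice with so few expected quitters. The change is worth making, but the point does not call the primary comparison's validity into question.

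**What to change.** - Delete the test-and-adjust rule, in both the general sentence and the quit-rate paragraph, together with the condition about power.
- Before outcomes are compared by arm, name two or three prognostic baseline covariates for the cluster-adjusted quit-rate model, to be included whatever the observed balance. Candidates are baseline FTND or cigarettes/day, plus the self-efficacy item if it is confirmed as a baseline measure.
- State which single model is primary, clustering-only or covariate-adjusted, and report the other alongside it. This removes the conflict.
- Keep the existing baseline adjustment in the linear reduction models, and extend it to quit attempts if a baseline value exists. The article is unclear here: it calls the first two listed reduction measures available at baseline, and quit attempts is second in that list, but it then gives quit attempts a Poisson model with no named baseline term.
- Present baseline characteristics by arm descriptively, without p-values.

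The cost is analysis-plan wording only, with no new data or visits. The article reports 135 of 184 randomised and follow-up continuing, so at that stage the change could still precede the comparison of outcomes.

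### Cigarettes per day, quit attempts and FTND are compared between arms only among continuing smokers, a group formed after randomisation, so these secondary comparisons cannot show which intervention is better at influencing quitting

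*Protocol article*

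**What the plan says.** The Background section of the protocol article lists cigarettes/day, number of quit attempts and nicotine addiction as Aim 1 efficacy outcomes c, d and e. The primary Aim 1 outcome is 6-month cessation from self-report together with the cotinine test (Data analysis).

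For the three reduction outcomes, the same section sets the population: "These analyses will be conducted for those who continue to smoke and look at the number of cigarettes/day smoked", and the sentence goes on to name quit attempts and then FTND. It gives no between-arm analysis of them in all randomised participants.

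On models, it says: "The first two of these are quantitative measures available at baseline and at follow-up so will be analyzed by multiple linear regression", with baseline values as covariates and adjustment for clustering. Shortly afterwards it says: "Quit attempts is a count variable which will be analyzed by a Poisson regression (designed for analysis of counts").

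On interpretation, it says that significant differences in quit rates and in the quantitative measures "will indicate whether the Tobacco Tactics intervention is more effective in influencing quitting".

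Two other statements in the section bear on this. Intent to treat means that "subjects are considered to be in the condition to which they were randomized", however much of the intervention they used. For the cessation measure, "participants who cannot be reached or who fail to return the cotinine strip will be considered to be still smoking".

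**The concern.** Whether a participant still smokes at follow-up is what the interventions are meant to change. Selecting on it breaks the comparability that randomisation gave. If one arm produces more quitters, and quitters tend to be lighter or more motivated smokers, that arm's remaining smokers are on average heavier or more dependent. The arm that works better can then look neutral or slightly worse on cigarettes/day. Adjusting for baseline consumption removes only the part of the selection that baseline consumption captures.

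Quit attempts have a further problem. Every quitter made at least one attempt, it succeeded, and the restriction deletes it, more often from the arm with more quitters.

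At stake is the reading of three of the five outcomes listed under Aim 1, because the article draws a conclusion about quitting from analyses that exclude everyone who quit.

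**Working it through.** **The plan's own figures.** The article states no expected value or power for the reduction outcomes, so there is none to reproduce. The Power analysis section gives 92 per group and 80% power for a 16-point difference in quit rates, without a control rate. With the pooled two-proportion formula and no continuity correction, power at 92 per group is 81% for 10% v 26% and 78% for 12% v 28%. Control rates of 10% and 12% are therefore assumed below.

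**How many people are removed.**
- 10% v 26%: 92 × 0.10 ≈ 9 and 92 × 0.26 ≈ 24, so about 33 of 184.
- 12% v 28%: 92 × 0.12 ≈ 11 and 92 × 0.28 ≈ 26. About 81 and 66 remain.

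**Bias in cigarettes/day, simulation 1.** All inputs except the 16-point difference are assumptions: quit rates 12% v 28%; mean 16 and SD 7 cigarettes/day; baseline to follow-up correlation 0.5; log-odds of quitting falling by 0 to 1.5 per SD of latent dependence. There are 2,000,000 people per scenario. Contrasts are website minus quit line. The first two result columns assume no true effect among continuing smokers.

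| Selection slope | Smokers only, unadjusted | Smokers only, baseline-adjusted | Baseline-adjusted, true effect −0.25/day |
|---|---|---|---|
| 0 | 0.00 | 0.00 | −0.24 |
| 0.5 | +0.33 | +0.16 | −0.07 |
| 1.0 | +0.63 | +0.32 | +0.08 |
| 1.5 | +0.80 | +0.43 | +0.19 |

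Without selection there is no bias. With it, baseline adjustment roughly halves the bias. A true reduction of 0.25/day changes sign at slopes 1.0 and 1.5. A true reduction of 0.5/day keeps its sign after adjustment but shrinks to −0.15 and −0.05.

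**Simulation 2, different assumptions.** Quit rates are 10% v 26%. Baseline is normal with mean 17 and SD 8. Follow-up is 0.7 × baseline + 3 − 2.5U + error, where U is motivation. The logit of quitting is c + U − 0.05 × (baseline − 17). Treatment acts only through quitting. The baseline-adjusted smokers-only contrast is about +0.3/day. With all randomised and quitters at 0 it is about −2.0/day.

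**Size against noise.** In simulation 1 the residual SD is about 7 × √(1 − 0.5²) = 6.06. The standard error is 6.06 × √(1/81 + 1/66) ≈ 1.0/day, ignoring clustering. Simulation 2, with an error SD of 4 to 6, gives 0.76 to 1.06. For a bias of 0.43, the chance of a significant result against the better arm is P(Z > 1.96 − 0.43) ≈ 6.3%, where 2.5% would occur by chance. For 0.16 it is about 3.6%.

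**What the all-randomised contrast measures.** With no selection and no reduction among smokers, it is 0.16 × 16 ≈ 2.6/day in favour of the website, matching the simulated −2.56. Across the simulation 1 scenarios it runs from −2.1 to −2.9.

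**Model assignment.** The listed order is cigarettes/day, quit attempts, FTND. The first two therefore go to linear regression, the second also goes to Poisson, and the third goes to nothing.

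**Who counts as a continuing smoker.** The section uses two cessation definitions, one cotinine-supported and one by self-report alone. A self-reported quitter who returns no strip is a smoker under the first and a quitter under the second. The reduction paragraph does not say which applies.

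**The case against.** The strongest reply is that these analyses are secondary and are introduced as a look at reduction short of quitting, which is a question about people who still smoke. If treatment works only through quitting, a near-zero smokers-only result is close to the right answer to that question, and the all-randomised figure is largely the quit effect restated. The bias is also a fraction of a standard error. All of this stands, and it limits the seriousness of the point. It does not rescue the comparison: the question explains a descriptive table of continuing smokers, but not a between-arm test read as evidence about quitting.

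The model conflict is most plausibly a slip, with the first two meant to be the two non-count measures, cigarettes/day and FTND. That is likely, and easily corrected.

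Some stronger readings are tempting but unsupported:
- **That intent to treat is contradicted.** The article defines it by assigned condition, and these analyses still compare arms as assigned.
- **That unreached people are put into this analysis without data.** The rule counting them as smoking is stated for the cessation measure only.
- **That the Poisson p-value must be too small.** That needs overdispersion, for which the article gives no figure, and the article already places Poisson regression within a mixed-model framework.
- **That a better intervention would generally look harmful.** This needs selective quitting and a small or absent true effect among smokers, and a significant result in that direction would be uncommon.

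**Conclusion.** The point holds as a weakness of three secondary Aim 1 analyses. The smokers-only contrasts are not randomised comparisons and cannot support the stated conclusion about influencing quitting. The expected bias is about +0.2 to +0.4 cigarettes/day against the arm with more quitters after baseline adjustment. This assumes a 16-point quit difference and that lighter or more motivated smokers quit more readily; without that selection it is zero. The size of the distortion in quit attempts cannot be calculated from the article. Its mechanism is certain: about 9 to 11 quitters in one arm and 24 to 26 in the other, each with at least one attempt, would be left out at the assumed rates. The primary cotinine-confirmed quit rate is not affected. The model assignment is inconsistent as written and needs correcting, whatever its cause.

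**What to change.** 1. Make the between-arm test of cigarettes/day (0 for quitters) and quit attempts (a successful quit counted as an attempt) an analysis of all randomised participants with follow-up data, with the baseline value and a training-session cluster effect.
2. State how FTND is scored in quitters, or report FTND descriptively.
3. Keep the smokers-only results as description, and say whether continuing to smoke is judged by self-report or by the cotinine-confirmed definition.
4. Name one model per outcome: a linear mixed model for cigarettes/day and FTND, and a count mixed model for quit attempts, with a negative binomial form if the counts are overdispersed.
5. Limit the concluding sentence about quitting to the analyses that include quitters.

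The cost is mainly wording, since the trial already plans to measure these outcomes. The Power analysis section reports 135 randomised, with recruitment and follow-up ongoing. The article does not say that quitters are asked about attempts, so the follow-up survey should be checked for this. The price is that the all-randomised contrast partly restates the quit effect, and the report should say so.

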#### Randomization and access to the intervention

Since there is a high probability for cross-contamination within training sessions, randomization will occur by training group (all individuals attending a specific training will be randomized to the same arm). The instruction sheet will give them information for logging on to the Tobacco Tactics website or calling the 1-800-QUIT-NOW telephone quit line. All subjects will be given time to make this first contact with the intervention during the training session where they will have access to a computer or telephone. After participating in the web-based Tobacco Tactics intervention, participants may continue to access the website from home, but this is not necessary as repeated access has not always been shown to increase efficacy of web-based interventions [25]. Both the intervention and control group will receive follow-up telephone calls. Both interventions are described in detail below.

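### Quit attempts, a secondary Aim 1 count, are assigned to Poisson regression with no allowance for likely overdispersion; given the planned session effect, the cost is small

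*Protocol article*

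**What the plan says.** Under Data analysis, the smoking-reduction outcomes are analysed among participants who continue to smoke: cigarettes per day, quit attempts and the FTND score, in that order. For the second of these the text reads "Quit attempts is a count variable which will be analyzed by a Poisson regression (designed for analysis of counts) with treatment condition", continuing "as the independent variable, controlling for covariates as needed". It mentions no dispersion check and no alternative model.

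Four other statements bear on this:

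- **Theoretical framework.** Of the Health Belief Model constructs, the protocol says "these characteristics are associated with 6-month quit rates and quit attempts". No size of association is given.
- **Data analysis, general rule.** "Clustering by group will be accounted for in analysis by using Generalized Linear Mixed Model variations of logistic regression, linear regression, and Poisson regression".
- **Randomization and access to the intervention.** "randomization will occur by training group (all individuals attending a specific training will be randomized to the same arm". Treatment is therefore a session-level variable.
- **Data analysis, Aim 2.** For the process measures, "Distributions will be examined before selecting the appropriate analytic method for comparison of groups". No such check is promised for quit attempts under Aim 1.

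The model is also not assigned cleanly. Just before the Poisson sentence, the text sends the first two listed measures to multiple linear regression. By list order, quit attempts is one of those two.

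**The concern.** A Poisson model sets the variance equal to the mean. If beliefs such as self-efficacy shift a person's expected number of attempts, expected counts differ between people in the same arm, and the spread of counts will usually exceed their mean. The beliefs are measured, but covariates enter only as needed, and the general rule in Data analysis ties adjustment to baseline differences between groups rather than to prediction of the outcome. The heterogeneity may therefore stay in the residual.

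If the model does not allow for it, the standard error of the treatment effect is too small, the confidence interval too narrow and the false-positive rate above the stated 5%. The protocol reads significant differences on the Aim 1 measures as showing whether the website is more effective, so this could feed an efficacy statement. The distribution check covers the process counts but not this one.

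**Working it through.** **Plan's own figures.** The plan gives no mean, variance, dispersion or power for quit attempts. Its Aim 2 power reproduces: 92 per group and a standardised difference of 0.5 (assumed meaning of medium) give 92.4%, against 92% stated. Its Aim 1 power is close if the control quit rate is 10% (assumed; not stated): 81.2%, against 80%. Neither figure bears on this count.

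**Inputs.** From the protocol: two-sided alpha 0.05, treatment at session level, Poisson mixed model. Assumed: 150 continuing smokers of the 184, mean 2 attempts, variance-to-mean ratio φ of 2 to 5, and 16 to 70 sessions in all.

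**Step 1: session effect omitted.** The model's z statistic is too large by √φ, so the two-sided error is 2 × [1 − Φ(1.96/√φ)]:

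- φ = 2: 2 × [1 − Φ(1.386)] = 16.6%
- φ = 3: 2 × [1 − Φ(1.132)] = 25.8%
- φ = 5: 2 × [1 − Φ(0.877)] = 38.1%

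**Step 2: why the session intercept matters.** A session with m smokers has total variance mμφ, an excess of (φ − 1)mμ over Poisson. A random intercept with variance σ² adds about (mμ)²σ². The two match when σ² ≈ (φ − 1)/(mμ). With 30 sessions, m = 150/30 = 5, so μ = 2 and φ = 2 give σ² ≈ 1/10. The model therefore reads person-level excess as session variance. Because treatment varies only between sessions, that variance enters its standard error.

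**Step 3: simulation under no treatment effect.** Negative binomial counts, unequal session sizes, 2,000 runs per row (Monte Carlo standard error about 0.5 to 0.7 points for the mixed-model columns). Entries are two-sided error in %.

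| Sessions (total) | φ | True session SD | No session effect | Poisson mixed, z | Poisson mixed, t |
|---|---|---|---|---|---|
| 16 | 2 | 0 | 17.7 | 10.0 | 7.2 |
| 16 | 3 | 0 | 25.8 | 8.9 | 6.3 |
| 30 | 2 | 0 | 16.7 | 7.4 | 5.8 |
| 30 | 3 | 0 | 23.9 | 7.1 | 5.9 |
| 60 | 2 | 0 | 16.4 | 6.4 | 5.8 |
| 60 | 3 | 0 | 25.1 | 5.8 | 5.1 |
| 16 | 1 | 0.3 | 26.6 | 8.6 | 6.2 |
| 30 | 1 | 0.3 | 19.7 | 7.1 | 6.0 |

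At 30 sessions and φ = 2 the true SD of the estimate is 0.173. The Poisson standard error without a session effect is 0.117 (0.117/0.173 = 0.68). With the session intercept it is 0.162 (0.94). At φ = 3 the mixed-model figure is 0.206 against 0.215 (0.96).

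The last two rows have no person-level overdispersion, yet show similar excess. Much of what remains is therefore a few-sessions effect.

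**Step 4: does a negative binomial mixed model help?** Same data for both models, no true session effect, z test, 800 runs per cell (Monte Carlo error about 1 point). Error in % at φ = 2, 3, 5:

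| Sessions per arm | Poisson mixed | Negative binomial mixed |
|---|---|---|
| 10 | 6.4, 8.9, 8.9 | 4.4, 5.9, 4.6 |
| 18 | 6.8, 4.9, 7.8 | 4.4, 3.5, 6.0 |
| 35 | 5.3, 5.3, 9.0 | 4.4, 4.0, 4.5 |

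The negative binomial is lower in all nine cells. With truly Poisson counts both models gave 3.4 to 3.9%. With a true session SD of 0.3 and 10 sessions per arm both gave 9.6%. A further set of runs at φ = 2 to 3 gave about 5 to 9% for Poisson and 4 to 8% for negative binomial, with little or no gain at session SD 0.3.

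**The case against.** A reader might infer that the counts are overdispersed, that the planned standard error is therefore too small, and that the false-positive rate is 17 to 38%. The documents do not support that reading.

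- **It describes a different model.** Those rates belong to Poisson regression without a session effect. The general rule specifies analysis "by using Generalized Linear Mixed Model variations of logistic regression, linear regression, and Poisson regression", and quit attempts is the one outcome expressly assigned to Poisson. The quit-attempts sentence does not repeat the clustering adjustment as the logistic and linear sentences do, but the general rule governs it. This objection stands.
- **Overdispersion is inferred, not shown.** Differing expected counts force the variance above the mean only if each person's count is itself about Poisson. Attempts that cannot overlap in time could vary less. The linked beliefs are measured and might be adjusted for. This stands too: overdispersion is likely, not established.
- **The remaining excess is largely a few-sessions effect.** This stands in part. The negative binomial model was lower at every fixed number of sessions, so some of the excess comes from the Poisson assumption. That comparison generated negative binomial data without session variation, which favours the proposed model, and the gain largely disappeared when session variation was added.
- **The outcome is secondary, and dispersion checks are often left to an analysis plan that is not shown.** The primary focus is 6-month cessation with cotinine, so the stakes are low. But the article does name a model for this count, and promises a check for the Aim 2 measures only.

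**Conclusion.** The point holds in a limited form. Quit attempts among continuing smokers are assigned to Poisson regression with no allowance for overdispersion, which the protocol's own account of attempts makes likely. With the session random intercept that the protocol requires, two-sided error is roughly 5 to 9% at assumed variance-to-mean ratios of 2 to 3 (10.0% in one 16-session layout with a z test), and part of that excess would remain under any count model with few sessions.

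These figures rest on assumed values for the number of continuing smokers, mean attempts, dispersion, and number and size of sessions, none of which the protocol gives. The benefit of changing the model is small and concerns a secondary measure. Severity: minor, optional.

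**What to change.** In Data analysis, replace the quit-attempts sentence with one stating that attempts among continuing smokers will be compared by negative binomial regression with a training-session random intercept, treatment as the independent variable, and baseline quit attempts as a covariate if these are collected. The model reduces to Poisson when there is no overdispersion.

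In the same edit, name the measures that go to linear regression instead of referring to the first two in the list, so that quit attempts has one model only.

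The cost is one extra dispersion parameter and a slightly wider interval for this outcome if counts are overdispersed, with no new participants. The change does not cure the few-sessions effect. In the simulations a t reference distribution reduced that more directly (10.0% to 7.2% at 16 sessions and φ = 2), but that choice is separate from the count model.
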